   1. PRIMARY OBJECTIVE

Main objective: to evaluate whether if an assisted weaning strategy based on SBT-PS with PEEP followed by an SBT-TP to identify patients at high risk of extubation failure and trigger the use of prophylactic post-extubation NIV (assisted weaning strategy, intervention group) leads to a **shorter time to successful extubation** in difficult to wean patients as compared to a weaning strategy based solely on SBT-TP (unassisted weaning strategy, control group) and prophylactic post-extubation NIV based on international guidelines

- 1. SECONDARY OBJECTIVES

1. To evaluate whether if an assisted weaning strategy leads to a higher rate of first successful extubation in difficult to wean patients as compared to an unassisted weaning strategy.
2. To evaluate whether if an assisted weaning strategy leads to a shorter duration of invasive mechanical ventilation in difficult to wean patients as compared to an unassisted weaning strategy.
3. To evaluate whether if an assisted weaning strategy leads to a shorter duration of mechanical ventilation (i.e., invasive and non-invasive) in difficult to wean patients as compared to an unassisted weaning strategy.
4. To evaluate whether if an assisted weaning strategy leads to more ventilator-free days (VFD) at day-28 and at day-90, respectively, in difficult to wean patients as compared to an unassisted weaning strategy.
5. To evaluate whether if an assisted weaning strategy leads to a shorter intensive care unit stay in difficult to wean patients as compared to an unassisted weaning strategy.
6. To evaluate whether if an assisted weaning strategy leads to a shorter hospital stay in difficult to wean patients as compared to an unassisted weaning strategy.
7. To evaluate whether if an assisted weaning strategy leads to a lower mortality in intensive care unit (ICU), mortality at day-28 and mortality at day-90, respectively, in difficult to wean patients as compared to an unassisted weaning strategy.
8. To evaluate whether if an assisted weaning strategy leads to a higher reintubation rate in difficult to wean patients as compared to an unassisted weaning strategy.
9. Background/Introduction
   1. STUDY DESIGN

- The study is a monocentric prospective open labelled, randomized controlled superiority trial, with two parallel groups and balanced randomization stratified into 3 groups (according to patients prior diseases), with a 1:1 ratio, using random blocks of size 4, 6 and 8.
- Type of control : alternative strategy
- Level and method of blinding : none (open labelled study)
- Method of treatment assignment: randomization with stratification
- Number of subject : 94 patients (47 per group)
- Duration of study : 90 days
  1. TREATMENT GROUPS

In this study, two strategies of weaning are compared: “assisted strategy” (intervention group) and “unassisted strategy” (control group).

Allocation sequence will be computer generated with stratification into 3 groups:

- Patients with chronic heart failure (CHF) (defined by an ejection fraction <45%)

- Patient with COPD or chronic respiratory failure

- Other patients

Randomization was done in each stratum with random blocks of size 4, 6 and 8.

Allocation sequence was concealed in a sealed opaque envelope with sequential number in each stratum. Allocation sequence was generated by a person independent from the investigator and not enrolling nor assigning patients to intervention.

Clinicians and investigators are enrolling patients and assigning patients to intervention according to the allocation.

Due to the type of intervention, no blinding is possible for the clinicians and the patients. During the database cleaning process, the statistician will be blind of the treatment allocation.

Patients are secondary excluded of the study if:

- Patient is transferred to another ICU
- Consent withdrawal
- Severe adverse event due to the study (on clinician decision)

These patients will be replaced.

- 1. STUDY POPULATION

Inclusion criteria:

• Patient 18 years old or more

• Intubated and ventilated in intensive care unit for more than 24 hours

• Patient ready for weaning evaluation

• Failure of a first SBT-TP

Exclusion criteria:

• Chronic neuromuscular disease

• Guillain-Barré Syndrome

• Central nervous system disease with consciousness disorder (i.e inability to obey a simple command)

• Tracheostomy

• Chronic disease with life expectancy less than 1 year

• Pregnancy, breast feeding

• Withholding life support regarding a reintubation

• Prisoner or patient interned in psychiatric hospital

• Under legal protective measures

• Language barrier

• Lack of social security

• Lack of the patient's consent (or of the next of kin where appropriate)

• Patient under an exclusion period after enrolment in another research study

- 1. INTERVENTION

The interventions will be started within the 6hr following inclusion.

Intervention group (assisted weaning strategy)

While intubated and being able to perform a SBT, patients will perform a daily SBT with pressure support 7 cmH2O and PEEP 5 cmH2O during at most 30 min to assess readiness to be weaned from mechanical ventilation. Inspired oxygen fraction (FiO2) is set between 21% to 50% in order to target a peripheral oxygen saturation (SpO2) between 94 and 98% (or between 88 and 92% for chronic obstructive pulmonary disease (COPD)/chronic respiratory failure (CRF) patients). SBT success is defined by the ability to perform the SBT-PS during 30 min without failure criteria. In case of SBT failure, patient is switch back to previous respiratory parameters. In case of SBT success, an additional SBT-TP will be performed after 30 min of rest, for a maximal duration of 30 min, to further assess the risk of respiratory failure at atmospheric pressure. The modalities of the SBT-TP are the same as the control group (see below). If the patient meets extubability criteria on SBT-PS (see below), he will be extubated 2 to 3 h after resuming ventilation and will receive post-extubation NIV unless contraindicated if SBT-TP was a failure or if meeting at least one of the following post-extubation prophylactic NIV criteria: age > 65 yrs., chronic heart failure (CHF), CRF, carbon dioxide partial pressure in arterial blood (PaCO2) > 45 mmHg during SBT, or COPD.

Control group (unassisted weaning strategy)

While intubated and being able to perform a SBT (Table 2), patients will perform daily a 30 min SBT by disconnecting the patient from the ventilator and using a T-piece to administer 0 to 10 L/min oxygen targeting a peripheral oxygen saturation (SpO2) between 94 and 98% (or between 88 and 92% for COPD/CRF patients). SBT success is defined by the ability to perform the SBT-TP during 30 min without failure criteria. In case of SBT failure, patient is switch back to previous respiratory parameters. If the patient succeeds the SBT-TP and meets extubability criteria, he will be extubated 2 to 3 h after resuming ventilation and will receive post-extubation NIV if meeting post-extubation NIV criteria (cf. supra) unless contraindicated.

- 1. SAMPLE SIZE

In a pilot observational study on 88 patients, median time between first SBT and extubation was 22h with a strategy using SBT-PS and PEEP. We hypothesized that a between-arm difference of at least 24 hours would be clinically relevant to prefer a SBT strategy over one another. With an alpha risk of 5% and a bilateral hypothesis, a power of 80% and a hazard ratio of 2 (based on the ratio of median duration of time between first SBT and successful extubation), a total of 66 successful extubation would be needed. Accounting for both potential deaths before successful weaning and weaning failure (assumed to amount to 30%), we plan to include 94 patients (47 per group).

- 1. STUDY PROCEDURE

|  | Inclusion (day-1) | Day-2 to day-90 | ICU discharge / Death | Day-28 | Day-90 |
| --- | --- | --- | --- | --- | --- |
| Demographic data | X |  |  |  |  |
| Patient weaning readiness | X | X* |  |  |  |
| SBT result | X | X* |  |  |  |
| Arterial blood gas | X | X* |  |  |  |
| *If SBT success* |  |  |  |  |  |
| Cough score | X | X* |  |  |  |
| Abundancy of respiratory secretions | X | X* |  |  |  |
| Extubability criteria | X | X* |  |  |  |
| *If extubation* |  |  |  |  |  |
| Extubation date and time | X** | X** |  |  |  |
| Extubation type (protocolized/self-extubation) | X** | X** |  |  |  |
| Post-extubation NIV characteristics | X** | X** |  |  |  |
| Respiratory physiotherapy characteristics | X*** | X*** |  |  |  |
| High-flow nasal oxygen use | X | X*** |  |  |  |
| Invasive mechanical ventilation status | X | X*** |  |  |  |
| *If reintubation* |  |  |  |  |  |
| Reintubation criteria | X | X |  |  |  |
| *If tracheostomy performed* |  |  |  |  |  |
| Characteristics of tracheostomy |  |  | X |  |  |
| *Follow-up data* |  |  |  |  |  |
| Date/hour of cessation of invasive ventilation and NIV |  |  | X |  |  |
| End of study |  |  |  |  |  |
| Respiratory status |  |  | X | X | X |
| Mortality |  |  | X | X | X |
| *As long as the patient is intubated or tracheostomized  **On the day of extubation and the day after  ***during the 7 days following extubation  NIV denotes non-invasive ventilation, and SBT spontaneous breathing trial. | | | | | |

1. Population of Analysis (intention to treat population)

All subjects who were randomized except patients secondary excluded from the study due to:

- Transfer to another ICU not participating to the study
- Consent withdrawal
- Lack of inclusion criteria or presence of exclusion criteria

All the analyses (including primary efficacy analysis) will be performed on this population.

1. Outcome Variables

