**TERTIARY OUTCOMES**

- Tracheostomy during ICU stay: categorical variable: Yes or no
  - Time of tracheostomy: date variable. Expressed as date (DD/MM/YYYY) and hour (HH:MM)
  - Method of tracheostomy: categorical variable. Percutaneous or surgical
  - Indication(s) for tracheostomy: categorical variable:
    - Difficult weaning: yes or no
    - Swallowing disorder/abundant bronchial secretions: yes or no
    - Other: yes or no
  - Patient successfully weaned from ventilation: yes or no
    - If yes: Time of successful weaning: date variable. Expressed as date (DD/MM/YYYY) and hour (HH:MM)
- End of protocol: categorical variable. Secondary exclusion or end of protocol
  - Date of study end: date variable. Expressed as date (DD/MM/YYYY)
  - In case of secondary exclusion: categorical variable. Transfer to another ICU not participating to the study; Consent withdrawal; In case of serious adverse event, according to the clinician in charge.
  - In case of end of protocol (Cause of end of protocol): categorical variable. No reintubation in the 7 days following extubation; Withdrawing of care or withholding of reintubation decision; ICU discharge ; death ; patient still intubated at Day 90.
- Severe adverse event: categorical variable. Yes or no.
- Respiratory status at ICU discharge (Day 28, Day 90): categorical variable. Not ventilated, non-invasive ventilation (except CPAP), invasive ventilation (tracheostomy), invasive ventilation (intubated), tracheostomy (without ventilation), dead, lost to follow up
- Date of ICU discharge: date variable. Expressed as date (DD/MM/YYYY)
- Date of hospital discharge: date variable. Expressed as date (DD/MM/YYYY)
- Successful extubation: categorical variable. Yes, death or weaning failure
- Successful extubation rank. Discrete variable. NA in case of death
- Time of successful extubation: date variable. Expressed as date (DD/MM/YYYY) and hour (HH:MM).
- Number of reintubation: Discrete variable

1. Statistical Methodology

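### The analysis set labelled intention to treat drops randomised patients, secondary exclusions are replaced, and the protocol's exclusion lists conflict, so the open-label comparison can be biased

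*Protocol*

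**What the plan says.** Section 3 of the protocol (Population of Analysis), headed as the intention-to-treat population, consists of "All subjects who were randomized except patients secondary excluded from the study due to" three reasons: "Transfer to another ICU not participating to the study", withdrawal of consent, and "Lack of inclusion criteria or presence of exclusion criteria". The next sentence fixes its scope: "All the analyses (including primary efficacy analysis) will be performed on this population".

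Section 2.2 (Treatment Groups) has its own list of secondary exclusions: transfer to another ICU, withdrawal of consent, and "Severe adverse event due to the study (on clinician decision". It adds: "These patients will be replaced". The same section states that "no blinding is possible for the clinicians and the patients".

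Section 4.3 (Tertiary Outcomes) codes the end of protocol. Under secondary exclusion it offers transfer, withdrawal, and "In case of serious adverse event, according to the clinician in charge", without requiring that the event be due to the study. The same section lists severe adverse event as a yes/no variable, and Section 5.2.5 compares it between arms. Section 5.2.2 puts the number and cause of secondary exclusions in the flow-chart.

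**The concern.** An intention-to-treat set keeps every randomised patient in the allocated arm. This one does not. Two of its three reasons for removal, transfer and withdrawal, arise after randomisation. The trial is monocentric (Section 2.1), so any other ICU is a non-participating one.

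Transfer is not clearly independent of the strategy. A patient who weans slowly stays longer and has more time in which to be transferred. Departures are also treated unequally. Under Section 4.1, an extubated patient who leaves the ICU within 7 days counts as a success. A still-intubated patient who moves to another ICU is deleted and replaced. An extubated patient moved to another ICU fits both rules.

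If removals depend on both arm and prognosis, the arms are no longer comparable, and replacements drawn from new admissions do not restore the balance. The primary hazard ratio, mortality and reintubation rate all rest on this set. Separately, the lists do not settle whether a patient excluded for an adverse event is analysed, so two analysts following the protocol could build different datasets.

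**Working it through.** **1. The lists side by side**

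| Reason | Section 2.2 (excluded and replaced) | Section 3 (leaves the analysis set) | Section 4.3 (end-of-protocol code) |
|---|---|---|---|
| Transfer | any other ICU | non-participating ICU | non-participating ICU |
| Consent withdrawal | yes | yes | yes |
| Adverse event | severe, due to the study | not listed | serious, no attribution required |
| Eligibility error | not listed | yes | not listed |

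The substantive conflict is between Section 3 and the other two. Read literally, Section 3 keeps a patient excluded for an adverse event in the analysis, although Section 2.2 has also recruited a replacement. An ineligible patient leaves the analysis, but no replacement is foreseen.

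**2. The plan's own sample size**

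Inputs (Section 2.5): hazard ratio 2, two-sided 5%, power 80%, 30% without the event.

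- Schoenfeld events: 4 × (1.960 + 0.842)² / (ln 2)² = 65.35, rounded up to 66, as stated.
- Patients: 66 / 0.70 = 94.3, stated as 94.

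The arithmetic reproduces. The 30% covers deaths and weaning failure, with nothing for exclusions.

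**3. Is replacement needed for power?**

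Keeping all 94 randomised patients gives 94 × 0.70 = 65.8 events and power 0.803. Removal without replacement would give 0.794 (2 removed), 0.781 (5) and 0.762 (9). With everyone kept in the analysis, replacement is not needed.

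**4. How large could the bias be?**

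The number of exclusions is not given, so it is assumed, as are their arm and outcome. The model has no true effect and 47 patients per arm. Of these, 70% are extubated with exponential times (median 22 + 24 = 46 h) and 30% never are. Patients are removed and replaced by random new ones, and the arms are compared by a log-rank test (4,000 simulated trials for the intervention-only rows, 8,000 for the others).

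| Removed and replaced | Hazard ratio | Chance of significance favouring intervention |
|---|---|---|
| none | about 1.00 | about 3% |
| 2 failures, intervention only | 1.08 | about 5% |
| 3 failures, intervention only | 1.12 | about 7% |
| 5 failures, intervention only | 1.21 | 13% |
| 3 failures intervention, 2 control | 1.04 | 4.9% |
| 3 failures in each arm | 1.00 | 3.3% |
| 3 intervention patients at random | 1.00 | 2.6% |

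The mechanism can be checked by hand. Each arm expects 47 × 0.70 = 32.9 successes. Replacing 3 failures adds 3 × 0.70 = 2.1 expected successes, so the intervention arm goes from 70% to 35.0 / 47 = 74.5%. Replacing 5 adds 3.5, giving 36.4 / 47 = 77.4%.

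A harsher model, with death as a competing event and the longest times removed from the intervention arm, gives hazard ratios of 1.16 (2 removed) and 1.35 (5 removed). Its two-sided rejection rates are 10.2% and 21.4%, against 5.9% with none removed. The result depends heavily on who is removed.

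**The case against.** Three objections carry weight.

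First, a reader might infer that the plan strips study-related severe adverse events out of the analysis and so empties the safety table. The documents do not support that. Section 3 does not name adverse events as a reason for leaving the analysis set, and the Section 4.3 item is a data code that defines no population. Even if Section 2.2 governed, only events that led to exclusion would be lost. Other severe adverse events would stay in the table, and the flow-chart would show the exclusions by cause. What stands is the ambiguity. If these patients are left out, their events drop out of the between-arm comparison and appear only as flow-chart counts.

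Second, a reader might take the hazard ratios of 1.12 to 1.21 as the expected bias. They are a worst case in which only failures, and only in one arm, are removed. Balanced or prognosis-free removal leaves the hazard ratio at about 1.00. The plan can bias the comparison; nothing in the documents shows that it will.

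Third, an eligibility error is a fact from before randomisation, and excluding on such facts need not bias anything. That is fair, but Section 3 does not say who judges eligibility or whether they are blind to arm and outcome, and the resulting set is still not intention to treat.

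**Conclusion.** The point holds and should be corrected before analysis, because the set governs the primary result and every other comparison. Two findings need no assumption: the set labelled intention to treat omits randomised patients, and the exclusion lists in Sections 2.2, 3 and 4.3 disagree on adverse events and eligibility errors.

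The size of any bias is conditional. With 3 to 5 intervention-arm failures removed and replaced (6% to 11% of 47) and no true effect, the hazard ratio is about 1.12 to 1.21 and the chance of a false positive favouring intervention is 7 to 13% instead of about 3%. This rests on assumed counts, constant hazards and one-sided selective removal, and it vanishes when removal is balanced or unrelated to outcome.

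**What to change.** - Reconcile Sections 2.2, 3 and 4.3 into one list with one wording for transfer and for adverse events, and state for each reason whether the patient is analysed.
- Define the primary analysis set as all randomised patients in their allocated arm. Use withdrawn patients' data up to withdrawal where consent allows.
- Obtain extubation and vital status to day 90 for transferred patients and for those excluded for an adverse event. Where this cannot be obtained after a transfer, censor at transfer and state that the censoring may be informative, since transfer may reflect the course of weaning.
- Do not let replacements substitute for randomised patients in the analysis. The 94 patients already give about 66 events and 80% power at the planned event share.
- Report severe adverse events in all randomised patients.
- Keep the reconciled exclusion set, relabelled modified intention to treat, as a sensitivity analysis only. Exclude eligibility errors only there, judged on pre-randomisation facts by someone blind to arm and outcome.

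These changes concern who is analysed and followed, not how any patient is treated. They cost wording changes and follow-up calls for a few patients.

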   1. PRIMARY OUTCOME

The primary outcome will be duration (in hours) between study inclusion and successful extubation (defined by the absence of reintubation or death within the 7 days (168 hours) following extubation). Reintubation and resuming of mechanical ventilation for less than 24h related to unplanned surgical procedure will not be considered as extubation failure. Patients extubated but exiting ICU within the 7 days following extubation will be considered as successful extubation. In patients not meeting extubation success criteria, data will be censored at day-90 or date of death whichever comes first.

- 1. SECONDARY PARAMETERS OUTCOMES

1. Rate of first successful extubation: number of patients successfully extubated after their first extubation/total number of patients per group
2. Invasive mechanical ventilation duration (expressed in hours): total cumulative time spent on invasive mechanical ventilation since inclusion per group. Each time period spent on invasive mechanical ventilation from inclusion until successful extubation are summed up. Patients not experiencing successful extubation will be censored at Day 90 or time of death (if earlier than Day 90).
3. Mechanical (invasive and non-invasive) ventilation duration (expressed in hours): total cumulative time spent on invasive and non-invasive mechanical ventilation since inclusion per group.
   - If the patient is successfully extubated with post-extubation NIV: date/time of NIV cessation minus date/time of inclusion. (or date/time of ICU discharge If NIV not ceased at ICU discharge)
   - If the patient is successfully extubated without post-extubation NIV: date/time of successful extubation minus date/time of inclusion.
   - Patients not experiencing successful extubation will be censored at Day 90 or time of death (if earlier than Day 90).
4. Ventilator-free days (VFD) at Day-28 and Day-90. VFD will be computed as follows from the day of inclusion:
   - VFD = 0 if the patient dies between inclusion and day-28 for VFD at day-28, or if the patient dies between inclusion and day-90 for VFD at day-90
   - VFD = 28-x for VFD at day-28 or VFD = 90-x for VFD at day-90 if the patient is successfully weaned from invasive mechanical ventilation, with x being the number of days from inclusion to last successful extubation. Successful weaning from mechanical ventilation will be defined as extubation without reintubation within at least 7 days (or weaning from mechanical ventilation for at least 7 days for patients with tracheostomy)
   - VFD = 0 if the patient is mechanically ventilated for more than 28 days after inclusion for VFD at day-28, or more than 90 days after inclusion for VFD at day-90
5. ICU stay (days): ICU length of stay between inclusion and ICU discharge
6. Hospital stay (days): hospital length of stay between inclusion and hospital discharge (to home or rehabilitation facility).
7. ICU, day-28, and day-90 mortality: defined as the ratio of the number of death over each period over the total number of patients per group.
8. Reintubation rate: number of patients with any reintubation divided by the number of patients per group

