  1. PRIMARY DATA ANALYSES

5.2.1 Outcome variables

5.2.1.1 Primary outcome

Primary outcome (time to successful extubation) is subjected to competitive risk (death). However, assuming competing risk will be identical in both groups, survival analysis will be done according to a cause-specific analysis (Cox model) with randomization strata as covariate. Hence, primary outcome will be assessed with the Hazard Ratio (HR) produced by Cox model.

Time to event will be:

- For patients successfully extubated: time from inclusion to successful extubation
- For patients who died before successful extubation or Day 90: time from inclusion to death, with censoring at this time point
- For patients not weaned from mechanical ventilation at Day 90 will be censored at this time point.

Two diagnosis will be performed:

1. Proportional hazard assumption will be checked through scaled Schoenfeld residuals statistical test and graphical plot
2. Verification of influential observations: outliers will be identified by 1) plotting deviance residuals and checking symmetrical distribution around zero and 2) plotting the estimated changes in the regression coefficients upon deleting each observation in turn (dfbeta) . In case of influential observation, the observation will be checked for error, corrected if wrong, or conserved if true.

If the proportional hazard assumption is not met, a chronological variable will be used, if possible, otherwise, a log-rank test will be performed.

To account for competing risk, a sensitivity analysis will be performed on the main outcome as follows: the main outcome will be described with cumulative incidence functions and analyzed with a Fine and Gray model with successful extubation as event and death as competitive risk, with randomization strata as covariate. Proportional hazard assumption will be checked by plotting Schoenfeld residuals against event time for each covariate. If the proportional hazard assumption is not met, a chronological variable will be used, if possible.

We will provide graphical representation using a Kaplan Meier curve for the Cox model, depicting the two groups without stratification and a cumulative incidence graph for Fine and Gray model depicting the two groups without stratification, with successful extubation and death as events.

Results will be reported a table with four columns (intervention group, control group, Hazard ratio, p-value). The subgroup analysis will be presented as a forest plot.

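### As written, the ICU-exit rule in the primary outcome counts a patient as successfully extubated even when death or reintubation within 168 hours is known

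*Protocol*

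**What the plan says.** Section 4.1 measures time from inclusion to successful extubation, which is "defined by the absence of reintubation or death within the 7 days (168 hours) following extubation". Two operating rules follow in the same paragraph. The first is a bounded exception: "Reintubation and resuming of mechanical ventilation for less than 24h related to unplanned surgical procedure will not be considered as extubation failure". The second concerns ICU exit: "Patients extubated but exiting ICU within the 7 days following extubation will be considered as successful extubation". For everyone else, "In patients not meeting extubation success criteria, data will be censored at day-90 or date of death whichever comes first".

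Section 5.2.1.1 repeats the censoring for the Cox model: "For patients who died before successful extubation or Day 90: time from inclusion to death, with censoring at this time point". The Fine and Gray sensitivity analysis takes successful extubation as the event and death as the competing event.

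In section 4.2 the ventilator-free-days (VFD) item has its own wording: "Successful weaning from mechanical ventilation will be defined as extubation without reintubation within at least 7 days". It does not mention ICU exit. In section 4.3 the causes of end of protocol are listed as "No reintubation in the 7 days following extubation; Withdrawing of care or withholding of reintubation decision; ICU discharge ; death", followed by still being intubated at day 90. ICU discharge is thus recorded separately from completing seven days without reintubation.

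**The concern.** The definition and the exit rule classify some patients in opposite ways. Someone who is extubated, goes to the ward and then dies or is reintubated before 168 hours fails the definition and passes the exit rule. The exit rule is not limited to patients whose later status is unknown, and nothing elsewhere in the protocol limits it. Applied literally, it overrides information that the trial holds.

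This touches the primary endpoint. Such a patient enters as an event at the extubation time instead of being censored at death or staying at risk after reintubation. The competing-risk sensitivity analysis uses the same event and so offers no protection. Secondary outcomes built on successful extubation, such as the rate of first successful extubation, may inherit the same coding.

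**Working it through.** **1. The plan's own figures.** Section 2.5 gives a hazard ratio of 2, two-sided alpha of 5%, 80% power, 66 successful extubations, a 30% allowance and 94 patients.

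- Schoenfeld events, 1:1 allocation: 4 × (1.960 + 0.842)² / (ln 2)² = 65.3, rounded up to 66.
- Patients: 66 / (1 − 0.30) = 94.3, against 94 stated.

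Both reproduce and are not in dispute.

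**2. One patient under each rule.** The patient leaves the ICU on day 3 after extubation and has the event on day 5.

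| Rule | Death on day 5 | Reintubation on day 5 (not the surgical exception) |
|---|---|---|
| 168-hour definition (4.1) | Failure | Failure |
| ICU-exit rule (4.1) | Success | Success |
| Cox model under the exit rule | Event at extubation | Event at extubation |
| Cox model under the 168-hour definition | Censored at death | At risk until a later successful extubation, death or day 90 |
| Fine and Gray under the exit rule | Event of interest | Event of interest |
| VFD (4.2) | 0 if death falls before day 28 or day 90 | Unclear (see below) |

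The censoring rule for deaths does not help. It applies to deaths before successful extubation, and under the exit rule that point has already been reached.

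VFD after reintubation is unclear for this reason: the seven-day wording has no exit rule, but the days are counted to the last successful extubation, a term that section 4.1 defines with the exit rule attached.

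**3. Number affected.** The protocol gives neither rate needed, so both are assumptions: 20–80% of counted successes leave the ICU within 7 days, and 3–10% of those die or are reintubated before 168 hours.

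- Low: 66 × 0.20 × 0.03 = 0.4
- Middle: 66 × 0.60 × 0.05 = 2.0
- High: 66 × 0.80 × 0.10 = 5.3

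**4. Power if those events were lost entirely.** Power = Φ(½ × √d × ln 2 − 1.960), where d is the number of events.

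| Events d | Power |
|---|---|
| 66 | 80.4% |
| 65 | 79.8% |
| 64 | 79.2% |
| 62 | 77.9% |
| 61 | 77.2% |

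**5. One-sided misclassification.** The simulation used 47 per arm, no true effect, exponential times with a median of 46 h (22 + 24, from section 2.5), 30% non-successes censored at day 90, and 1,500 runs. A share of the intervention arm's non-successes (47 × 0.30 = 14.1 patients) was recoded as success at the extubation time. A hazard ratio above 1 favours the intervention.

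| Share recoded | Patients | Mean hazard ratio | Two-sided rejection |
|---|---|---|---|
| 0 | 0 | 0.99 | 4.5% |
| 10% | 1.4 | 1.07 | 5.7% |
| 20% | 2.8 | 1.17 | 9.2% |
| 40% | 5.6 | 1.36 | 25% |

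The simulation error on 4.5% is √(0.045 × 0.955 / 1500) = 0.5 percentage points, so the step to 5.7% is barely distinguishable from noise. The last row puts 5.6 patients in one arm, more than the 5.3 assumed above for both arms together. The table shows sensitivity to an extreme imbalance and is not a forecast. The arms were labelled arbitrarily; loading the control arm would move the ratio the other way.

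**The case against.** The strongest reply is that section 4.1 states a general definition and then prespecified conventions, and that a specific rule may qualify a general one. ICU discharge is its own end-of-protocol cause, so the exit rule may have been meant for patients no longer observed daily. That is a plausible intention, but the text does not confine the rule to such patients. The surgical exception beside it shows that limits were written where they were wanted.

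Three stronger readings are tempting and are not supported.

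- **That the rule conceals deaths and reintubations from the trial.** It does not. Day-28 and day-90 mortality, VFD and the reintubation rate are separate outcomes. Deaths remain in the first two, and reintubations in the third if recorded after discharge.
- **That discharging sooner improves the primary outcome.** Event time runs to extubation, so earlier discharge shortens no true success. Only patients who are extubated, leave and then fail inside the same 168 hours matter. Transfers to a non-participating ICU are outside the analysis population (section 3).
- **That the rule favours the intervention.** The assisted arm can extubate after a failed T-piece trial and has an additional trigger for non-invasive ventilation (section 2.4). Secondary objective 8 contemplates more reintubation there. Yet extra ventilation support could delay ICU discharge and so expose more of that arm's failures. No section gives discharge timing by arm.

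It is also fair that the power figures overstate the loss, because a reintubated patient may still be successfully extubated before day 90. That event would be delayed, not removed.

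**Conclusion.** The point holds on the wording of the protocol, the only document available here. An unconditional rule classes as success some patients whom the 168-hour definition classes as failures, and neither planned primary analysis corrects this. Confidence is high on the wording and low on the size.

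The range of about 0.4 to 5 of 66 events rests wholly on assumed rates. The effect on power is minor. Distortion in favour of one arm would need these failures to be unequal between arms. In an open-label trial that is possible, and with 66 events a few patients can matter, but the documents support no statement on direction. The VFD inconsistency is an ambiguity to settle, not a demonstrated contradiction. The change is worth making because the rule sits in the primary endpoint and is easy to repair.

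**What to change.** In section 4.1, apply the 168-hour definition wherever vital and ventilatory status after ICU exit is known. A known death or reintubation within 168 hours, other than the stated surgical exception, is then a failure whether or not the patient has left the ICU. Limit the exit rule to early leavers with no known event or with unknown status at 168 hours. State that the same rule governs first successful extubation and VFD. Report by arm how many patients left before 168 hours, how many had a known later event and how many had unknown status. Add a sensitivity analysis using the exit rule as it now stands.

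Much of the information is already planned. Mortality and respiratory status are collected at day 28 and day 90, invasive ventilation status is scheduled for the 7 days after extubation (section 2.6), and the Cox model needs time of death. The cost is a record check for patients who leave the ICU before 168 hours, which a single-centre trial should manage, and possibly slightly fewer or later events. Some statuses will stay unknown, and unrecorded failures among them would still count as successes; this is why the number should be shown by arm.
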